### Data management

We will use a custom-built and secure REDCap database. All study documentation will be stored securely in either locked filing cabinets (paper files) or electronically (electronic database files) with access granted only to authorised study team members. Logic and range checks will be used to minimise data entry errors and to identify missing data and other problems. To ensure confidentiality, the final dataset will contain deidentifiable information only. All publications associated with the study results will involve deidentified data to maintain participant confidentiality. Demographic information linking the participant to the data will be stored in a separate file. Only the principal investigator will have access to this information after the study.

### Sample size

A total of 240 participants (120/group) will provide 80% power to detect a 0.9 point between-group difference in 12-point SPPB scores at 6 months (assuming SD of 2.8, p=0.05, and 20% dropouts). A 0.5 point between-group difference in SPPB is considered to be clinically significant.^30^ This sample size is expected to be sufficient to detect between-group differences of 10–15% for the secondary outcome measures. These calculations used the *sampsi* command in Stata V.13 and PASS V.13 and allow for a 20% loss to follow-up.

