#### Secondary outcomes

The secondary outcomes will include: (1) rate of falls using the internationally recognised fall definition: ‘an unexpected event in which the participant comes to rest on the ground, floor, or lower level, as a result of a loss of balance”^25^; (2) five times sit-to-stand test will be analysed as an standalone predictor of future disability in older people^26^; (3) quality of life will be measured by the EuroQol 5 dimensions five level health questionnaire (EQ-5D-5L) enabling participants to rate their level of impairment across mobility, self-care, usual activities, pain/discomfort, and anxiety/depression and give a global health rating on a visual analogue scale (EQ-VAS), the EQ-5D-5L was found to be a highly reliable and valid measure of the quality of life in older people with mild to moderate dementia^27^; and (4) individualised mobility goal attainment will be measured with the Goal Attainment Scale (GAS) where participants and/or their ‘person responsible’ will identify a key goal related to physical functioning, the GAS is recommended as a measure of relevant person-centred outcomes in the evaluation of complex interventions in older people.^28^

*Cost-related outcomes* will include intervention delivery costs (from study records, including staff salary, travel and equipment costs) and health service utilisation costs (from calendars and aged care documentation records) during the trial period.

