### Data analysis

The primary analysis will be based on an intention-to-treat approach. The primary effectiveness outcome will be assessed as a change in participants' mobility using the SPPB. It will be treated as a continuous variable. The effect of group allocation on the outcome at 6-month follow-up will be analysed using linear regression models with baseline scores entered into the linear regression model as a covariate. Alternatively, if distributions are overly skewed (on visual inspection of histograms), the change scores (post-pre) will be analysed. The number of falls per person year will be analysed using negative binomial regression models to estimate the between-group difference in fall rates after 6 months with exposure entered as the offset variable.^31^ The other secondary continuous outcomes (five times sit-to-stand test and EQ-5D-5L) will be analysed using regression models with baseline variables as covariates as described for the primary outcome.^31^ Ordinal regression will be used to compare groups on the GAS.

Prespecified subgroup analyses will use interaction terms (group × outcome) in the model to explore whether there is a differential effect of the intervention in residential aged care facilities versus community-dwelling residents and in those with more marked cognitive impairment. Secondary analyses using causal modelling maybe conducted to establish intervention effects in people with greater exercise dose.^32^

Cost-effectiveness will be explored as the cost per extra person avoiding mobility deterioration as defined as an improvement or no change in the 12-point SPPB score between baseline and 6 months. Cost-effectiveness analysis may also be conducted on falls (ratios will be calculated relative to the control group for the incremental cost per fall avoided per person) and the quality-adjusted life year (QALY) gained (calculated from EQ-5D-5L). Bootstrapping will estimate a distribution around costs and health outcomes and calculate the CIs around the incremental cost-effectiveness ratios. The results will be plotted on the cost-effectiveness plane, and as cost-effectiveness acceptability curves. These methods have been used previously when calculating the incremental cost-effectiveness ratios for exercise programmes for older people.^33^

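### The statement that the sample can detect 10–15% differences in the secondary outcomes is wrong for rate of falls

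*Protocol article*

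**What the plan says.** The Sample size section first gives the primary calculation: "A total of 240 participants (120/group) will provide 80% power" for a 0.9-point difference on the Short Physical Performance Battery, with the inputs "assuming SD of 2.8, p=0.05, and 20% dropouts". It then adds: "This sample size is expected to be sufficient to detect between-group differences of 10–15% for the secondary outcome measures". It says that the calculations "allow for a 20% loss to follow-up". No inputs are given for the secondary claim, and no secondary outcome is excepted.

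The Secondary outcomes section opens its list with "rate of falls using the internationally recognised fall definition". The Data analysis section fixes the method for this outcome: "negative binomial regression models to estimate the between-group difference in fall rates after 6 months", with exposure as the offset. The article states neither a control-group fall rate, nor a dispersion, nor a separate power calculation for falls.

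**The concern.** One percentage is offered for four kinds of secondary outcome: an event rate, a timed test, a quality-of-life score and an ordinal goal scale. For an overdispersed count over half a year in about 100 people per arm, a 10–15% change in rate is very small relative to the sampling error of the log rate ratio.

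Falls matter to this trial. The introduction names mobility and falls together as the evidence gap, and the conclusion lists fall reduction among the things the trial will examine. A reader who takes the sample size sentence at its word could conclude that a non-significant fall-rate ratio excludes a 15% reduction, although the trial would most likely miss a reduction of that size.

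**Working it through.** **The plan's own figure.** The 10–15% cannot be reproduced, because no inputs are given for it. It can only be tested against the stated design.

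**Inputs from the article.** 120 per arm randomised 1:1; 20% loss, so 120 × 0.8 = 96 per arm; significance level 0.05 (taken as two-sided, since sidedness is not stated); 80% power (the level stated for the primary outcome); 6 months of follow-up, or 0.5 person-years; negative binomial model with an exposure offset. People lost part-way contribute some exposure, so 96 and 120 per arm bracket the truth.

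**Assumed inputs, not in the article.** Control rate 1–5 falls per person-year, and dispersion k from 0.5 to 2. The case k = 0 (Poisson, no overdispersion) is the most favourable bound.

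**Formula.** With μ = rate × 0.5 and rate ratio RR, Var(log RR) = (1/n) × [1/μ + 1/(μ·RR) + 2k]. Power follows from |log RR|/SE against 1.96, counting both tails.

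**One cell in full.** Rate 1.5, so μ = 0.75; k = 1; RR = 0.85; n = 96.
- Bracket: 1.333 + 1.569 + 2 = 4.902. SE = √(4.902/96) = 0.226.
- |log 0.85| = 0.1625, and 0.1625/0.226 = 0.719.
- Power = Φ(0.719 − 1.960) + Φ(−0.719 − 1.960) = 0.107 + 0.004 = 0.111.
- Number needed for 80% power: 7.849 × 4.902/0.02641 ≈ 1,457 analysed per arm, where 7.849 = (1.960 + 0.842)² and 0.02641 = (log 0.85)².

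**Power (%) for a 15% reduction, 96 per arm (120 per arm in brackets)**

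| Falls per person-year | k = 0 | k = 0.5 | k = 1 | k = 2 |
|---|---|---|---|---|
| 1 | 11.9 (13.7) | 10.6 (12.0) | 9.7 (10.9) | 8.5 (9.4) |
| 2 | 19.0 (22.6) | 14.5 (17.0) | 12.2 (14.0) | 9.8 (11.1) |
| 3 | 26.2 (31.5) | 17.4 (20.6) | 13.7 (16.0) | 10.5 (11.9) |
| 5 | 40.0 (47.9) | 21.4 (25.6) | 15.6 (18.3) | 11.1 (12.7) |

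**Rate ratio detectable with 80% power, 96 per arm (120 per arm in brackets)**

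| Falls per person-year | k = 0 | k = 0.5 | k = 1 | k = 2 |
|---|---|---|---|---|
| 1 | 0.50 (0.54) | 0.46 (0.51) | 0.43 (0.48) | 0.38 (0.43) |
| 2 | 0.63 (0.67) | 0.58 (0.61) | 0.53 (0.57) | 0.47 (0.51) |
| 3 | 0.69 (0.72) | 0.62 (0.66) | 0.57 (0.61) | 0.50 (0.54) |
| 5 | 0.76 (0.78) | 0.67 (0.70) | 0.61 (0.64) | 0.52 (0.56) |

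**Two bounds that do not depend on the grid** (80% power, RR 0.85)
- No overdispersion: μ = 7.849 × (1 + 1/0.85)/(96 × 0.02641) ≈ 6.7 falls per person in 6 months, about 13.5 per person-year. With 120 per arm it is 5.4 in 6 months.
- Unlimited fall rate: k ≤ 96 × 0.02641/(2 × 7.849) ≈ 0.16. With 120 per arm it is 0.20.

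**Alternative reading: percentage points of people who fall.** With 30–60% fallers in the control group and 96 per arm, power is 28–36% for 10 points and 55–71% for 15 points. It comes close to 80% only for 15 points from 30%, with no loss at all (79.8% at 120 per arm). This is also not the planned outcome, which is a rate.

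**The case against.** The best defence is that the sentence is hedged as an expectation, concerns secondary outcomes only, and affects no sample size, model or primary analysis. The Data analysis section already describes the falls model as one that estimates a difference, and nothing in the article says that a non-significant result will be read as no effect. All of this stands. It limits the weight of the point but does not make the sentence true for falls.

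Several stronger readings are tempting, and the article does not support them:
- **Power is about 10%, or only a halving is detectable.** These describe particular cells of the tables. The article gives neither rate nor dispersion, so only ranges can be stated.
- **The sentence is wrong for every secondary outcome.** This is not shown. For the five times sit-to-stand test and EQ-5D-5L, 96 per arm detects 10–15% of the mean if the SD is at most about 25–37% of the mean unadjusted. With an assumed baseline correlation of 0.6 the limit is 31–46%. The article gives no means or SDs to check this.
- **The figure has no meaning for the Goal Attainment Scale.** A difference in percentage points of people attaining their goal is an ordinary reading. Not saying which reading is meant is imprecision, not error.
- **The cost per fall avoided is compromised.** That analysis is optional, rests on bootstrapped distributions and intervals, and takes no input from the power sentence.

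**Conclusion.** The point holds for rate of falls and no further. The Sample size section gives the design a property that it does not have for its first-listed secondary outcome. Under the assumed 1–5 falls per person-year and k of 0.5–2, the chance of detecting a 15% reduction is roughly one in eleven to one in four, and below one in two even with no overdispersion and no loss. A 10% reduction is harder still. The exact power depends on assumptions that the article does not supply. That 80% power is out of reach does not, short of about 5.4–6.7 falls per person in 6 months or an outcome with almost no overdispersion. The sentence is wrong as written, but it concerns a secondary outcome and the correction is one of wording. It casts no doubt on the primary analysis.

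**What to change.** In the Sample size section:
- Limit the 10–15% sentence to the outcomes for which it was actually calculated, and say what the percentage refers to.
- For falls, state the rate ratio detectable with 80% power, with the sponsor's own control rate and dispersion assumptions. The ranges above illustrate the scale and should not be copied in as the figure.
- Add that falls are not powered for a 10–15% difference and will be interpreted from the rate ratio and its 95% CI, so that a non-significant result is not read as excluding an effect of that size.

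The cost is text only. Sample size, model and conduct stay as they are. The stated capability for falls becomes less favourable.

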### Data analysis

The primary analysis will be based on an intention-to-treat approach. The primary effectiveness outcome will be assessed as a change in participants' mobility using the SPPB. It will be treated as a continuous variable. The effect of group allocation on the outcome at 6-month follow-up will be analysed using linear regression models with baseline scores entered into the linear regression model as a covariate. Alternatively, if distributions are overly skewed (on visual inspection of histograms), the change scores (post-pre) will be analysed. The number of falls per person year will be analysed using negative binomial regression models to estimate the between-group difference in fall rates after 6 months with exposure entered as the offset variable.^31^ The other secondary continuous outcomes (five times sit-to-stand test and EQ-5D-5L) will be analysed using regression models with baseline variables as covariates as described for the primary outcome.^31^ Ordinal regression will be used to compare groups on the GAS.

Prespecified subgroup analyses will use interaction terms (group × outcome) in the model to explore whether there is a differential effect of the intervention in residential aged care facilities versus community-dwelling residents and in those with more marked cognitive impairment. Secondary analyses using causal modelling maybe conducted to establish intervention effects in people with greater exercise dose.^32^

Cost-effectiveness will be explored as the cost per extra person avoiding mobility deterioration as defined as an improvement or no change in the 12-point SPPB score between baseline and 6 months. Cost-effectiveness analysis may also be conducted on falls (ratios will be calculated relative to the control group for the incremental cost per fall avoided per person) and the quality-adjusted life year (QALY) gained (calculated from EQ-5D-5L). Bootstrapping will estimate a distribution around costs and health outcomes and calculate the CIs around the incremental cost-effectiveness ratios. The results will be plotted on the cost-effectiveness plane, and as cost-effectiveness acceptability curves. These methods have been used previously when calculating the incremental cost-effectiveness ratios for exercise programmes for older people.^33^

A detailed analysis of the implementation outcomes relating to the intervention’s reach, fidelity, dose delivered, adoption, feasibility and exercise adherence measures will be conducted. This data will be presented numerically and descriptively.^34^ Thematic analysis will be conducted for interview data.^35^ We will use the NASSS framework (Nonadoption, Abandonment and Challenges to the Scale-Up, Spread and Sustainability of Health and Care Technologies) to provide a conceptual ‘lens’ that will inform our implementation analysis. NASSS consolidates multiple implementation frameworks and empirical studies, targeting key issues relating to implementation and uptake of telehealth at the microlevel of individual staff and consumers, the mesolevel challenges of organisational engagement and adoption, and macrolevel policy and regulatory factors.^36^

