### Randomisation

Participant baseline data will be collected before randomisation. Two hundred and forty participants will be randomly assigned (1:1) to either the telehealth physiotherapy TOP UP exercise programme or to the wait-list control group. The trial will use a centralised web-based randomisation system using Research Electronic Data Capture (REDCap) within The Sydney Local Health District license to ensure concealment of group allocation. A research investigator not involved in baseline assessment measures or recruitment of facilities will develop a randomisation schedule. They will use a computer-generated random number schedule with randomly permuted block sizes of two and four. Allocation to either the intervention group or the control group will be stratified according to the participants’ place of residence (at home receiving aged care services or living in residential aged care).

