2.Why	Older people receiving aged care services have a high prevalence of mobility disability and a high rate of falls. Physiotherapy-led exercise programmes that increase leg strength and challenge balance are proven to improve mobility and reduce falls. Telehealth is emerging as an effective method to deliver physiotherapy to improve access in regional areas and during COVID-19.
3.What materials	Participants allocated to the TOP UP exercise programme will be provided with a mobile tablet with internet connectivity to access Zoom, online exercise videos and the StandingTall app. Participants will receive a booklet comprising descriptions of their home exercise programme based on the Otago exercise programme, an exercise and falls calendar, ankle weights (1 and 2 kg), details on how to access and connect to the online exercise programmes, and balance support such as a sturdy dining chair, kitchen bench, parallel bars or wall bar.
4.What procedures	TOP UP physiotherapists will deliver balance and strength exercise prescription advice and health coaching using telehealth. Participants will be supported to access zoom to videoconference with a physiotherapist and aim to exercise for 2 hours/week supported by TOP UP Coaches (trained care staff of the participant’s aged care service provider). The research team will provide the physiotherapists and TOP UP Coaches with a 2-hour training session on the study protocol at the beginning of the study.
5.Who provides	The intervention will be conducted by either the research team’s physiotherapists or other registered physiotherapists employed by the study’s aged care partners. All physiotherapists will have 3 years+ experience in working in aged care supervising care staff. TOP UP Coaches will be selected by the aged care service providers from their interested pool of care workers.
6.How	TOP UP Coaches will support the participant to gain access to the technology for the Zoom physiotherapy sessions, lead group exercise classes in residential aged care, and supervise weekly the individual exercise programmes using the participant exercise booklet, online exercise videos, and StandingTall app. Participants allocated to the wait-list control group will receive a similar 3-month intervention once the trial is completed.

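### Randomisation is stratified by place of residence, but the between-group models named in the protocol leave residence out, which gives up some precision

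*Protocol article*

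**What the plan says.** The Randomisation section describes individual 1:1 allocation in permuted blocks: "Allocation to either the intervention group or the control group will be stratified according to the" participant's place of residence, with two levels, home and residential aged care.

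The Data analysis section then names the terms of each between-group model:

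- **SPPB (primary):** "analysed using linear regression models with baseline scores entered into the linear regression model as a covariate". If distributions are too skewed, change scores are analysed instead.
- **Five times sit-to-stand and EQ-5D-5L:** regression with baseline values as covariates, on the pattern of the primary outcome.
- **Falls:** negative binomial regression with exposure as the offset. No covariate is named.
- **GAS:** ordinal regression comparing the groups. No covariate is named.

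Residence appears in the analysis once, as a prespecified subgroup interaction. The Data collection section adds that falls are self-recorded on calendars by home care participants, but are entered by TOP UP Coaches in the online documentation system in residential care.

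On delivery, Table 2 says that coaches in the intervention arm "lead group exercise classes in residential aged care, and supervise weekly the individual exercise programmes". Neither the Sample size nor the Data analysis section mentions an effect of coach, physiotherapist or class.

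**The concern.** Stratified blocks balance the arms within each setting, so the difference between settings drops out of the sampling variation of the treatment effect. A model without the stratum still counts that difference as residual noise. Its standard error is then larger than the design warrants, intervals are wider than they need be, and power is lost.

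Residence is likely to be prognostic here, since it separates people by frailty. For falls it also separates two recording routes, so recorded rates may differ by setting for reasons of measurement as well as risk. The falls and GAS models name no baseline covariate that could absorb any of this.

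The article does not leave covariates wholly to a later plan. It names them, and the factor on which allocation was balanced is not among them.

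**Working it through.** **1. The plan's own figure, and the residual SD it implies.** The Sample size section targets a "0.9 point between-group difference in 12-point SPPB scores at 6 months", "assuming SD of 2.8, p=0.05, and 20% dropouts", with 120 per group. That leaves 0.8 × 120 = 96 evaluable per arm.

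- Unadjusted SE = 2.8 × √(2/96) = 0.404.
- Two-sided power = Φ(0.9/0.404 − 1.96) = Φ(0.267) = 60.5%.
- The stated 80% is reached if the outcome is adjusted for a baseline score correlated about 0.607 with it. The residual SD is then 2.8 × √(1 − 0.607²) ≈ 2.226.

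The sample size is a separate matter. It is used here only to fix a range for the residual SD, 2.226 to 2.8.

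**2. SPPB.** Let s be the residual SD without the stratum, p the residential share, and b the difference between settings that remains after adjustment for baseline SPPB. The model without the stratum overstates the SE by the factor √[s² / (s² − p(1−p)b²)]. True type I error is then 2[1 − Φ(1.96 × factor)]. Neither p nor b is in the document; I assume p from 30% to 50% and b from 0.25 to 1.5 points.

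| s | p | b = 0.25 | b = 1.0 | b = 1.5 |
|---|---|---|---|---|
| 2.8 | 0.3 | 1.001 | 1.014 | 1.032 |
| 2.8 | 0.5 | 1.001 | 1.016 | 1.038 |
| 2.226 | 0.3 | 1.001 | 1.022 | 1.051 |
| 2.226 | 0.5 | 1.002 | 1.026 | 1.062 |

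Worked for the last cell: 2.226² = 4.955; 0.25 × 1.5² = 0.5625; √(4.955/4.3925) = 1.062. Across the table, true type I error runs from 5.0% down to 3.7%.

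Simulation check (192 evaluable, stratified blocks, 6,000 runs under the null, b = 1): mean model SE is 0.328 without residence and 0.320 with it, a ratio of 1.025. Rejection is 4.7% and 5.3%; the Monte Carlo error is about 0.3 points.

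**3. Falls.** Assumed: 48 evaluable per arm and setting, 0.5 years' exposure, rate ratio 0.6. Within a cell, the variance of the log rate is (1/μ + k)/48, with μ the expected count and k the dispersion.

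Case A: 1 versus 4 falls per person-year, k = 0.7.

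- Home (μ = 0.5 and 0.3): (2.000 + 0.7 + 3.333 + 0.7)/48 = 0.1403.
- Residential (μ = 2.0 and 1.2): (0.500 + 0.7 + 0.833 + 0.7)/48 = 0.0569.
- SE with residence = 1/√(1/0.1403 + 1/0.0569) = 0.201.
- Without residence, the dispersion takes up the spread between settings: k* = (0.7 × 2.125 + 0.5625)/1.25² = 1.312. SE = √[(1/1.25 + 1.312 + 1/0.75 + 1.312)/96] = 0.223.
- Ratio 0.223/0.201 = 1.11 by hand. Simulated (1,000 runs): 0.221 against 0.201, ratio 1.10. Power is 66% without and 73% with residence; rejection under the null is 3.9% and 5.3%.

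Case B: 1 versus 3 falls per person-year, k = 1.

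- SE with residence = 1/√(1/0.1528 + 1/0.0787) = 0.228.
- k* = (1 × 1.25 + 0.25)/1² = 1.5, and SE without = √[(1 + 1.5 + 1.667 + 1.5)/96] = 0.243.
- Ratio 1.07 by hand and 1.05 simulated. Power is 58% and 62%.

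The simulated ratios are the better guide, because the fitted dispersion does not match the moment formula exactly.

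**4. Clustering, for the optional analysis only.** With m participants per coach and correlation ICC in the intervention arm alone, the true SE exceeds the independence SE by √[(2 + (m−1)ICC)/2]. The document gives neither quantity. For m = 3 and ICC = 0.01 the factor is 1.005. For m = 12 and ICC = 0.10 it is 1.245. That range is too wide to support a conclusion.

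**The case against.** **For SPPB the gain is small and the error is on the safe side.** This stands. Baseline SPPB should carry much of the difference between settings, an even split is the case that maximises the effect, and type I error is not inflated.

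**The falls figures rest on assumed rates.** This also stands: no fall rate or dispersion is in the document. The direction does not depend on them; the size does.

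**Residence is already in the planned modelling.** Only in part. An interaction fitted for a subgroup question does not put residence in the model that gives the main result. It does show that the variable will be to hand.

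**The full analysis plan may add the stratum.** Possible, but the article lists the model terms, so the text as published should be corrected or confirmed.

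**A stronger reading.** A reader might infer that the models treat people who share coaches and classes as independent, so that standard errors are wrong in both directions. The documents do not support stating that as fact:

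- The article is silent on random effects and robust standard errors, and a condensed article may leave these to the full plan.
- It gives no caseload and no ICC.
- Group classes are placed in residential care and are one option among several, and controls may attend seated group classes under usual care.
- The two effects offset each other. Simulated together (1-point residence difference, ICC 0.05), type I error was 5.1% with 5 participants per coach and 6.6% with 10.

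What remains is that shared coaches and physiotherapists in the intervention arm are documented. That is reason enough for a sensitivity analysis, but not for a claim of error.

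**Conclusion.** The point holds as one of efficiency. The design stratifies on residence and none of the named main models includes it. Model standard errors will be somewhat too large wherever residence predicts the outcome beyond the covariates already named.

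- **SPPB:** about 0% to 6% of the SE, assuming a 30% to 50% residential share and 0.25 to 1.5 points of residual difference between settings.
- **Falls:** about 5% to 10% of the SE and roughly 4 to 7 points of power, assuming fall rates three to four times higher in residential care and equal strata.
- **Sit-to-stand, EQ-5D-5L and GAS:** same direction of loss, size not calculated. In the ordinal model for GAS, the loss would show mainly as an odds ratio drawn towards 1.

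The omission does not make the trial's conclusions invalid or anti-conservative. No conclusion about the size of clustering can be drawn from the document.

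**What to change.** Add place of residence as a fixed covariate in every between-group model: SPPB (including the change-score fallback), sit-to-stand, EQ-5D-5L, falls and GAS. State this before unblinding, so that the choice cannot depend on results. It costs one sentence and one parameter per model, and the variable is already recorded for randomisation.

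Optionally, prespecify one sensitivity analysis of the primary outcome that allows for clustering by coach or physiotherapist in the intervention arm only, for example a partially nested mixed model. Confirm that coach and physiotherapist identifiers are held with the outcome data. The cost is a possibly wider interval in that one analysis. If the full analysis plan already provides for this, nothing more is needed.

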**Method and analysis:**

This type 1 hybrid effectiveness-implementation randomised controlled trial will involve 240 people aged 65+ years receiving aged care services in community or residential settings. Participants will be randomised to either: (1) the Telehealth Physiotherapy for Older People (TOP UP) Program or (2) a wait-list control group. The 6-month intervention includes 10 physiotherapy sessions delivered by videocall (Zoom). The intervention will include the local support of an aged care worker and online exercise resources. Primary outcome is mobility at 6 months post randomisation measured by the Short Physical Performance Battery. Secondary outcomes include rate of falls, sit-to-stand, quality of life, and goal attainment at 6 months after randomisation. Regression models will assess the effect of group allocation on mobility and the other continuously scored secondary outcomes, adjusting for baseline scores. The number of falls per person over 6 months will be analysed using negative binomial regression models to estimate between-group differences. An economic analysis will explore the cost-effectiveness of the TOP UP programme compared with usual care. Implementation outcomes and determinants relating to the intervention’s reach, fidelity, exercise dose delivered, adoption, feasibility, acceptability, barriers and facilitators will be explored using mixed methods.

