#### Primary outcome

Mobility will be measured by the 12-point *Short Physical Performance Battery (SPPB*) test score. The SPPB measures standing balance, gait (2.44 m timed walk), and timed sit-to-stand (five repetitions). The SPPB has predictive validity showing a gradient of risk for mortality, nursing home admission and disability.^24^

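### The primary analysis may switch from baseline-adjusted regression to change scores on a threshold-free look at histograms; the switch is unnecessary and either does nothing or loses precision

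*Protocol article*

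**What the plan says.** In the protocol article, the Data analysis section says that the effect of allocation on the 6-month SPPB is to be "analysed using linear regression models with baseline scores entered into the linear regression model as a covariate". The next sentence provides a fallback: "Alternatively, if distributions are overly skewed (on visual inspection of histograms), the change scores (post-pre) will be analysed". The article sets no numerical criterion for skew. It does not say whether the histograms are of baseline scores, 6-month scores or residuals, whether they are pooled over arms, or whether baseline remains a covariate once change scores are used.

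Three other places bear on this.

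- The same paragraph introduces the outcome with the words "The primary effectiveness outcome will be assessed as a change in", although the first-choice model analyses the 6-month score.
- The abstract gives only the adjusted analysis and mentions no switch: "Regression models will assess the effect of group allocation on mobility and the other continuously scored secondary outcomes, adjusting for baseline scores".
- The Sample size section works on the 6-month score. It says that 240 participants "will provide 80% power to detect a 0.9 point between-group difference in 12-point SPPB scores at 6 months", and it states no baseline correlation.

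On the secondary outcomes, the section says: "The other secondary continuous outcomes (five times sit-to-stand test and EQ-5D-5L) will be analysed using regression models with baseline variables as covariates". It adds that they follow the approach given for the primary outcome, so the fallback plausibly extends to them.

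**The concern.** The estimator for the primary outcome should be settled before anyone sees the data that it will be applied to. Here it depends on whether someone judges a histogram to be too skewed, and two analysts could reasonably decide differently on the same data. This is a rule that the article states, so it is more than a detail left to the analysis plan.

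The fallback also has to earn its place. Linear regression makes its distributional assumption about residuals, and at this sample size inference on a group difference tolerates moderate skew. If the adjusted regression performs adequately under skew, the switch answers no real problem. What is then at stake is precision on the primary outcome, and having one primary result that was fixed in advance.

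**Working it through.** **Inputs.** From Sample size: 120 per group, 20% loss, SD 2.8, difference 0.9 points, p=0.05. Hence 120 × 0.8 = 96 analysed per group. Two-sided testing is assumed because sidedness is not stated. The correlation r is not in the article and is varied. Equal SDs at baseline and 6 months are assumed.

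**The plan's own figure.** Unadjusted, SE = 2.8 × √(2/96) = 0.404 and 0.9/0.404 = 2.227. Power = Φ(2.227 − 1.960) = 60.5%, not 80%. With the adjusted regression (ANCOVA), SD = 2.8 × √(1 − r²), and 80% is reached at r = 0.607. The stated power is therefore consistent with ANCOVA and an unreported r of about 0.61. A one-sided test with all 120 per group also gives 80.1%, but that contradicts the stated dropout.

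**Reading 1: baseline kept.** Write the ANCOVA model as Y = a + τG + βX + e, with Y the 6-month score, X baseline and G group. Subtracting X from both sides gives Y − X = a + τG + (β − 1)X + e. The values of τ and e are unchanged, so the estimate, its standard error and its p-value are identical. In simulated trials the rejection rates of the two models agreed exactly.

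**Reading 2: baseline dropped.**

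- ANCOVA variance: 2.8²(1 − r²)
- Change-score variance: 2.8² × 2(1 − r)
- Ratio: 2(1 − r)/(1 − r²) = 2/(1 + r), above 1 for every r below 1

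At r=0.6 the ANCOVA SD is 2.240, its SE is 0.323 and power is Φ(0.9/0.323 − 1.960) = 79.5%. The change-score SD is 2.504, its SE is 0.361 and power is 70.2%. Over the range, with 96 per group:

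| Assumed r | Variance ratio | ANCOVA power | Change-score power |
|---|---|---|---|
| 0.3 | 1.538 | 64.6% | 46.9% |
| 0.5 | 1.333 | 73.0% | 60.5% |
| 0.6 | 1.250 | 79.5% | 70.2% |
| 0.7 | 1.176 | 87.7% | 82.0% |
| 0.8 | 1.111 | 96.0% | 94.1% |
| 0.9 | 1.053 | 99.9% | 99.9% |

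At r of 0.6 to 0.607, restoring 80% power with unadjusted change scores would take a total of about 300 to 306 participants instead of 240.

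Uncorrected chance imbalance at baseline is this same loss and not a further one. At r=0.6 an imbalance of one SE (0.404) moves the change-score estimate by 0.4 × 0.404 = 0.16 points, and 0.323² + 0.16² gives back 0.361² within rounding.

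**Is the switch needed under skew?** Simulation: 4,000 trials per scenario, 96 per group, r=0.6 on the underlying normal scale, scores skewed and rounded to integers from 0 to 12.

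- Mean skewness with no effect: 0.69 for the 6-month score, 0.52 for ANCOVA residuals, about 0.00 for change-score residuals.
- ANCOVA type I error: 4.9% (Monte Carlo SE √(0.05 × 0.95/4000) = 0.3 points).
- Power for a 0.9-point shift: ANCOVA 83.2%, change score without baseline 74.0%.

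The adjusted analysis kept its error rate and was the more powerful of the two on skewed data.

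**The case against.** The strongest defence is that the trigger is the shape of a distribution and not the treatment effect. Under randomisation both estimators are unbiased for the same mean difference, and a blinded look at pooled data would do little harm. That stands, and it limits the severity. A reader might infer that the rule inflates the type I error. Choosing the smaller of the two p-values would raise it to about 6.7% to 7.4% in simulation, but the article does not propose that, so it is not a consequence of the plan as written.

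A second defence is that the article never says baseline is dropped. The preceding sentence includes it as a covariate and the abstract adjusts for it without exception. This also stands: the power loss is conditional. Under this reading, though, the fallback reproduces the adjusted analysis exactly and has no purpose.

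A third is that change scores can deal with skew. A reader might infer that they cannot, but that is wrong in general. When baseline and follow-up are similarly skewed their difference can be nearly symmetric, as it was in the simulation. The argument against the switch is that symmetry is not needed here.

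Finally, the article speaks only of distributions. It does not say that raw follow-up scores are the ones inspected, and it gives no SPPB data from which to judge how likely the trigger is.

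**Conclusion.** The point holds in a limited form and is a should-fix. The article leaves the primary estimator to an unspecified visual judgement, and the alternative is either identical to the adjusted regression or less precise. If baseline is dropped, the loss is about 9 percentage points of power at the r of about 0.6 that would account for the stated 80%. It is 12.5 points at r=0.5, under 2 points at r=0.8 and negligible at r=0.9. These figures rest on 96 analysed per group, SD 2.8 at both times, two-sided 0.05 and an assumed r. The robustness to skew rests on one simulated shape of moderate skew.

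Two stronger conclusions are not supported. One is that the trial will lose this power: that requires the trigger to be met, baseline to be dropped and r to be moderate, none of which the article settles. The other is that the 80% is wrong: ANCOVA with r of about 0.61 reproduces it.

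**What to change.** Delete the switch. State that linear regression of the 6-month SPPB on group, adjusted for baseline, is the only primary analysis whatever the distribution, with heteroscedasticity-robust or bootstrap confidence intervals. If reassurance about skew is wanted, name one sensitivity analysis in advance, label it as such and keep baseline in it; an ordinal model adjusted for baseline would serve. Reword the sentence that describes the primary outcome as a change, so that it matches the model. Apply the same rule to the five times sit-to-stand test and EQ-5D-5L.

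The cost is wording only, settled before unblinding. Sample size, data collection and trial conduct are unaffected, and precision can only stay the same or improve.
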